#### Covariate-adjusted analyses

This analysis will aim at establishing the improvements (in terms of outcome variables) due to the intervention. We will take into account the non-equivalence of the three intervention groups with respect to some baseline characteristics. This will be examined through logistic regression. Robust standard errors will be adjusted for clustering at village level. We will check and compare adjusted and unadjusted odds ratio while doing the logistic regression.

#### Asset index

An asset index will be constructed for the households by performing principal component analysis on key household characteristics like household ownership of house, a two wheeler and domestic animals, utilities used in the household like tap water inside their houses, access to electricity or access to other amenities [43, 44].

#### Difference in difference analysis

Difference in difference estimation will be used to test the effect of the intervention on the outputs. This analysis will adjust for the possibility of other factors like time, institutional factors leading to the output.

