**Methods:**

This study aims to understand if (and how) a package of interventions targeting primary health centres and community participation platforms affect utilisation and access to generic medicines for people with non-communicable diseases in the current district context in India. This study will employ a quasi-experimental design and a qualitative theory-driven approach. PHCs will be randomly assigned to one of three arms of the intervention. In one arm, PHCs will receive inputs to optimise service delivery for non-communicable diseases, while the second arm will receive an additional package of interventions to strengthen community participation platforms for improving non-communicable disease care. The third arm will be the control. We will conduct household and facility surveys, before and after the intervention and will estimate the effect of the intervention by difference-in-difference analysis. Sample size for measuring effects was calculated based on obtaining at least 30 households for each primary health centre spread across three distance-based clusters. Primary outcomes include availability and utilisation of medicines at primary health centres and out-of-pocket expenditure for medicines by non-communicable disease households. Focus group discussions with patients and in-depth interviews with health workers will also be conducted. Qualitative and process documentation data will be used to explain how the intervention could have worked.

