### Study design and conceptual framework

In this study, we use a quasi-experimental approach along with a theory-driven evaluation to study an intervention for improving access to medicines for diabetes and hypertension at PHCs in Tumkur district of Karnataka, India. We will use a quantitative before-after quasi-experimental study design to understand determinants of improved access to medicines, and a qualitative theory-driven evaluation approach to answer the *how* questions. All PHCs (39 PHCs) across three selected *talukas* were randomly assigned to one of three arms of the intervention. A baseline and an endline survey of households, PHCs and private pharmacies will be conducted for the before-after quasi-experimental component.

The qualitative component of the study will use a theory-driven approach to understand and explain the changes if any, and why the intervention worked for some (where it did) and not for others (where it did not) across the three arms of the study. The theory-driven approach uses successive waves of qualitative data to refine the programme theory, thus resulting in a contextual explanation for how the programme worked in the given setting [25]. In so doing, we shall generate an explanatory theory about improving access to medicines in local health systems in India especially focusing on what works, for whom, and under what conditions, and why. The study design and initial programme theory have been represented in Fig. 2 and Fig. 3. An initial programme theory is an explanation of why the programme is expected to work; it takes into consideration the inputs of the intervention and the assumptions of the implementers on how the intervention inputs could result in the expected outcomes, integrating contextual information from the implementation setting.

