**Fig. 5 Fig5:**
[figure not shown]
ATM conceptual framework

Of the seven *talukas* which qualified for the intervention, we randomly chose three *talukas* using the online random number generating tool (Available at http://www.random.org/; see Additional file 2). The three *talukas* chosen were Koratagere, Sira and Turuvekere. Some characteristics of the three *talukas* are presented in Table 2. PHCs across the three *talukas* were randomly assigned to one of three arms (A, B and C) of the study intervention. In Arm A, PHCs will receive a package of interventions to optimise service delivery, while Arm B, they will receive Arm A package as well as an additional package of interventions to strengthen existing community participation platforms for organising NCD care at PHC. PHCs in Arm C will be the control. The package of activities in A, B and C are described in Table 3. A detailed description of the intervention and the underlying assumptions behind the activities proposed is provided in Additional file 3 and step-wise plan of rolling out of the intervention is presented in Fig. 6.

**Table 2 Tab2:** Characteristics of study talukas

Characteristics	Koratagere	Sira	Turuvekere
Area	652 Sq km	1552 Sq km	778 Sq km
Population	160,952	301,473	174,297
Number of private pharmacies	19	30	22
General adult literacy rate	71 %	67 %	73 %
Number of PHCs	11	17	11
Average population per PHC	14,500	18,000	16,000
Number of private hospitals/clinics	21	64	18
Number of PHCs with qualified MBBS doctors (of) total number of PHCs in *taluka* (as on March 2014)	11 of 11	15 of 17	10 of 11

(Source: Census 2011)

**Table 3 Tab3:** Description of activities planned under the study intervention arms

Intervention arm	Intervention name	Intervention input	Activities
A	Optimise service delivery	Orientation training & workshop for PHC medical officers	Training on standard treatment guidelines for NCDs, rational prescription, maintaining treatment cards for patients with NCDs and conduction of health days for NCD care.
		Training workshop for pharmacists	Training on need assessment for medicines, counselling patients on medicines and their side effects and non- drug treatment, indenting for medicines and record keeping at PHCs.

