Turuvekere	11
Sira	17
Koratagere	11
Total	39

Geographic coordinates were captured for each of the household and facility surveyed using a hand-held global positioning system (GPS) device (GARMIN model EPX 300). This will enable generation of maps to summarise the household and facility data using QGIS, a geographic information system application that allows for geo-spatial data analysis and mapping (QGIS Version 2.4). There were PHCs where we could not sample cluster b and/or cluster c due to their small geographic spread (see Table 6). In other instances, we sampled sometimes in excess and sometimes lesser than desired number of households based on the availability of a NCD patients in these houses (see Fig. 8). The various households and facilities (PHCs and private) where data was collected are represented in Fig. 9. In some instances, where areas covered by a given PHC were smaller, we could only identify two distance-based clusters (a and b), as seen in Koratagere in Fig. 10. Similarly, the sampled households in Sira are shown in Fig. 11.

**Table 6 Tab6:** Distribution of sampled clusters (a, b and c) across the ATM study *talukas*

Taluka	Number of cluster a (<5kms)	Number of cluster b (5–10 km)	Number of cluster c (>10 km)	Total
Turuvekere	11	11	11	33
Sira	17	17	14	48
Koratagere	11	10	6	27
Total	39	38	31	108

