##### End-line survey

After 18 months of the intervention, the survey will be conducted in the same three talukas. The same households (panel survey) that participated in the baseline survey will be visited again with the survey questionnaire.

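### With randomised PHCs and a household panel, difference-in-difference is unbiased but less precise than adjusting the endline outcome for its own baseline value

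*Protocol article*

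**What the plan says.** **Allocation.** Study design and conceptual framework gives the randomised units: "All PHCs (39 PHCs) across three selected" talukas. The section on the rapid assessment and choice of talukas says that the PHCs "were randomly assigned to one of three arms (A, B and C) of the study intervention", with arm C as control.

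**Repeat measurement.** End-line survey: "After 18 months of the intervention, the survey will be conducted in the same three talukas", and "The same households (panel survey) that participated in the baseline survey will be visited again with the survey questionnaire". The PHCs are also surveyed as facilities before and after.

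**Estimator.** It is named twice. The abstract says the authors "will estimate the effect of the intervention by difference-in-difference analysis". The section Difference in difference analysis says "Difference in difference estimation will be used to test the effect of the intervention on the outputs", and adds that this allows for influences such as time and institutional factors.

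**Other adjustment.** Covariate-adjusted analyses plans a logistic regression: "We will take into account the non-equivalence of the three intervention groups with respect to some baseline characteristics". Standard errors there are clustered at the village. The baseline value of the outcome is not named as a covariate, and no section plans an endline outcome adjusted for its own baseline value.

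**The concern.** Difference-in-difference is most useful when arms were not formed by chance and may start at different levels. Here the PHCs were randomised, so baseline differences between arms are chance differences. A concurrent randomised control arm already deals with time trends, and randomisation balances institutional factors in expectation.

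Subtracting the baseline in full carries all of its noise into the estimate. When the baseline-endline correlation is below 1, only part of a chance baseline difference is expected to persist to endline, so removing all of it takes away too much. Over repeated randomisations this averages to zero. In any one trial it is extra error, and with 39 randomised units the arms can differ noticeably at baseline. What is at stake is the width of the confidence intervals and the power.

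**Working it through.** **The plan's own figures.** Planned sample: 30 households × 39 PHCs = 1170, as stated. Achieved baseline sample (Table 4): 326 + 482 + 261 = 1069, or 1069/39 = 27.4 households per PHC. The article has no power figure against which to set the estimator.

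**Assumptions.** The article gives neither the split of PHCs by arm nor r. I assume 13 per arm (39/3) and vary r. Let s² be the variance of a PHC-level value, equal at both rounds.

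**Variance per randomised unit.**
- Endline only: s²
- Difference-in-difference: 2(1−r)s²
- Endline adjusted for baseline: (1−r²)s²

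The ratio of adjusted to difference-in-difference is (1−r²)/[2(1−r)] = (1+r)/2. The excess carried by difference-in-difference is 2(1−r) − (1−r²) = (1−r)², in units of s². When r is below 0.5, 2(1−r) exceeds 1, so difference-in-difference is then less precise than ignoring the baseline altogether.

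| assumed r | variance ratio | interval narrower by | power of adjusted model where difference-in-difference has 80% (13 v 13) |
|---|---|---|---|
| 0.3 | 0.65 | 19.4% | 94% |
| 0.5 | 0.75 | 13.4% | 90% |
| 0.7 | 0.85 | 7.8% | 86% |
| 0.9 | 0.95 | 2.5% | 82% |

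**Cost of estimating the slope.** The table is a large-sample result. In 20,000 simulated trials of 13/13/13 PHCs, the variance ratio was 0.62 at r = 0.2, 0.77 at 0.5, 0.93 at 0.8, 0.98 at 0.9 and 1.00 at 0.95. Against the formula values 0.60, 0.75, 0.90, 0.95 and 0.975, that is a cost of about 3-4%. Multiplying the table's ratios by 1.03 to 1.04, the net variance reductions are about 32-33%, 22-23% and 12% at r = 0.3, 0.5 and 0.7. Both estimators averaged within 0.003 of a true effect of zero.

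**What r might be.** With m = 27.4 households per PHC, intracluster correlation ρ, PHC-level autocorrelation c and household-level autocorrelation h, the correlation of PHC means is

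r = [mρc + (1−ρ)h] / [1 + (m−1)ρ].

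For assumed ρ of 0.01 to 0.10, c of 0.5 to 0.8 and h of 0.3 to 0.6, r runs from 0.34 to 0.75. Intervals are then about 6% to 18% narrower, before the slope cost.

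**Error in a single trial.** A baseline imbalance of one standard error is s√(2/13) = 0.39s. Difference-in-difference removes (1−r) times that too much: 0.5 × 0.39 = 0.20s at r = 0.5.

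**The case against.** The strongest reply is that this is a preference for efficiency: difference-in-difference is a legitimate unbiased estimator, and the size of the loss rests on an r that nobody has stated. The unbiasedness stands, and the point is made only as one of precision. But the estimator is fixed explicitly, in the abstract and in the analysis section, so the choice has not been left to a fuller document.

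A second reply also stands in part. The formula is for continuous outcomes. The article reports risk and odds ratios, and Table 9 includes percentages, a change in a median and an incremental cost-effectiveness ratio. In logistic regression, adjustment changes the odds ratio being estimated, so the percentages above do not transfer directly. Exit-interview patients are not described as a panel. A household-level slope alone also need not deliver the PHC-level gain.

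A reader might infer stronger points that the article does not support:
- **That difference-in-difference biases the result.** It does not under randomisation; the over-correction is conditional on a chance imbalance.
- **That covariates will be picked from observed imbalance.** The sentence "We will take into account the non-equivalence of the three intervention groups with respect to some baseline characteristics" describes no selection rule, and a condensed article may leave the covariate list elsewhere.
- **That leaving out taluka and distance band is a serious omission.** Neither is shown to be a strong predictor, and effects that are constant over time cancel when a household or PHC is differenced from itself. The article notes "There were PHCs where we could not sample cluster b and/or cluster c due to their small geographic spread", and Table 6 implies 39 − 31 = 8 PHCs without a cluster beyond 10 km, but this has no bearing on the choice of estimator.
- **That the loss equals a fixed number of PHCs.** Any such figure depends on the assumed r.

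**Conclusion.** The point holds as a loss of precision that can be avoided at little cost, not as an error of validity. For continuous outcomes or PHC-level means with equal variances, baseline adjustment lowers the variance by about 35%, 25% and 15% at assumed r = 0.3, 0.5 and 0.7, less about 3-4% for the slope. The gain is small above r of about 0.8 and gone near 0.95. These figures rest on an r that the article does not give; the power and simulation figures also assume 13 PHCs per arm. For binary outcomes the direction of the advice is the same, but the size is not established here. The planned logistic regression does not settle the matter, because it neither names the baseline outcome nor replaces difference-in-difference.

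**What to change.** Fix the following before endline data are analysed:

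1. **Primary model**, for household and facility outcomes measured at both rounds: the endline outcome on arm, adjusted for its own baseline value. For household outcomes include both the household's baseline value and the PHC baseline mean; for facility outcomes, the PHC's baseline value. Taluka is an optional addition.
2. **Inference** clustered at the PHC, which is the randomised unit, in place of the village clustering given in Covariate-adjusted analyses.
3. **Exit-interview outcomes:** adjust only for the PHC-level baseline mean.
4. **Difference-in-difference** kept as a sensitivity analysis.

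The change is to wording only and needs no new data. It costs about one degree of freedom per PHC-level slope, and two more if taluka is added. Households missing at endline drop out of the adjusted model unless a constrained longitudinal model, with baseline means held equal across arms, is used.

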### Survey sampling

#### Quantitative data

##### Household survey

The WHO household survey tool does not have inclusion criteria related to NCD. Sample size calculation was based on obtaining at least 30 households per PHC spread across three clusters (a, b and c with 10 households per cluster; see above). A typical PHC in Tumkur district has at least five villages in each cluster, and hence at least 1000 households in each cluster (approximately 250 households in a village). We aimed for a total of 1170 households anticipating 30 households per PHCs across the 39 PHCs.

We started the survey at the PHC where we listed all the villages under the PHC area. These villages were then divided into the three clusters based on the distance from the PHC and from each cluster, one village was randomly chosen. We randomly selected a minimum of 10 NCD households from all four directions starting from the central point of the village. After getting informed consent of the participant the survey questionnaire was administered to the NCD patient for the interview. In his/her absence, the spouse or another member of the household who was over 18 years of age, aware of the information sought in the survey and willing to provide this information was interviewed. The data collectors started the survey within each village in four different directions and ensured that all types of houses and areas within the village were included in the sampling. Wherever 10 NCD households were not obtained in one village, the data collectors repeated the process in the nearest adjoining village. Each participant was provided with an information sheet and health awareness material in local language related to NCDs (Additional file 7) as well as contact information of the research team.

We surveyed 10 households from within five kilometre radius from the PHC (cluster a), 10 from between five to 10 km radius (cluster b), and 10 from more than 10 km distance from the PHC (cluster c). All of the 39 PHCs in these three *talukas* were covered, resulting in 1069 NCD households surveyed as presented in Table 4 and Table 5. The same households shall be sampled during the endline survey planned in last quarter of 2015.

**Table 4 Tab4:** Distribution of households participating in the study by *taluka*

S No.	Taluka	Number of households interviewed
1	Turuvekere	326
2	Sira	482
3	Koratagere	261
Total		1069

**Table 5 Tab5:** Number of PHCs covered in the ATM study talukas

Taluka	Number of PHCs

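### Difference-in-difference is a valid but inefficient main effect estimate for randomised PHCs measured at both surveys; an endline model adjusted for the baseline outcome would be more precise

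*Protocol article*

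**What the plan says.** Three statements in the protocol article matter together.

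- **Allocation.** Under Study design and conceptual framework, all 39 PHCs in the three talukas "were randomly assigned to one of three arms of the intervention". The abstract and the section on choosing talukas agree. The design is nonetheless called quasi-experimental.
- **Repeated measurement.** The End-line survey section says: "The same households (panel survey) that participated in the baseline survey will be visited again with the survey questionnaire". The Household survey section says the same, and the design section has PHCs surveyed at both times.
- **Estimator.** The abstract says the authors "will estimate the effect of the intervention by difference-in-difference analysis". The section on difference in difference analysis makes it the effect test: "Difference in difference estimation will be used to test the effect of the intervention on the outputs". It adds: "This analysis will adjust for the possibility of other factors like time, institutional factors leading to the output".

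The Covariate-adjusted analyses section adds logistic regressions that allow for arms differing on certain unnamed baseline characteristics. It does not name the baseline value of the outcome, and it does not say that these regressions replace DiD.

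**The concern.** DiD is the natural estimator when groups were not formed at random and fixed differences between them must be removed. Here allocation was random, so baseline differences between arms arise by chance. Subtracting the whole baseline difference is then more than is needed. If r is below 1, part of a chance gap would have disappeared by endline without any correction.

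At stake is the width of the confidence intervals. All PHCs in the chosen talukas are already in the study, so clusters cannot be added. The household target was set by coverage, with no power, intracluster correlation or effect size stated. The analysis is the remaining place to gain precision.

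**Working it through.** **The plan's own figures.** The article says: "We aimed for a total of 1170 households anticipating 30 households per PHCs across the 39 PHCs". 30 × 39 = 1170, which agrees. Table 4 gives 326 + 482 + 261 = 1069 households surveyed, or 1069/39 = 27.4 per PHC. No power calculation is stated, so none can be reproduced.

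**Assumptions.** There are 13 PHCs per arm (39/3; arm sizes are not stated), equal outcome variance at both times, a linear scale and complete pairs. The correlation r is not in the article, so a range is shown.

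**Variances**, relative to an analysis of the endline alone (= 1):

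- DiD: 2(1-r)
- Endline adjusted for baseline (ANCOVA): 1-r²
- Standard error ratio DiD/ANCOVA: sqrt(2(1-r)/(1-r²)) = sqrt(2/(1+r))

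**Effect of a chance gap.** Given a baseline gap g, the expected endline gap without any effect is r·g. DiD therefore returns r·g - g = -(1-r)g, while ANCOVA returns about 0.

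| r | SE ratio, formula | Interval width ratio, simulated, 13 PHCs per arm | DiD power where ANCOVA has 80% | DiD shift for a 10-point gap |
|---|---|---|---|---|
| 0.3 | 1.24 | 1.22 | 62% | 7 points |
| 0.5 | 1.15 | 1.14 | 68% | 5 points |
| 0.7 | 1.08 | 1.07 | 73% | 3 points |
| 0.9 | 1.03 | 1.01 | 78% | 1 point |

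The simulation used 20,000 replicates and t-intervals on 36 (DiD) and 35 (ANCOVA) degrees of freedom. Both estimators averaged to the true value. The slope of the DiD estimate on the baseline gap was -0.70, -0.50, -0.30 and -0.09; for ANCOVA it was about 0. Below r = 0.5, DiD is less precise than ignoring baseline: at r = 0.3, sqrt(2 × 0.7) = 1.18 against 1.00.

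**Plausible r for PHC means.** With m = 27.4 households per PHC, r = (m·ICC·CAC + (1-ICC)·w)/(m·ICC + 1-ICC). Here ICC is the intracluster correlation, CAC is the correlation of PHC effects over time, and w is the within-household correlation. Assume ICC 0.02 to 0.10, CAC 0.5 to 0.9 and w 0.3 to 0.5.

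- Lowest: (27.4×0.02×0.5 + 0.98×0.3)/(27.4×0.02 + 0.98) = 0.37, SE ratio 1.21
- Highest: (27.4×0.10×0.9 + 0.90×0.5)/(27.4×0.10 + 0.90) = 0.80, SE ratio 1.05

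**How likely is a gap?** Assume a baseline proportion of 20%. The standard error of a two-arm difference is sqrt(2×0.2×0.8×(ICC + (1-ICC)/27.4)/13), which is 4.6 points at ICC 0.05 and 5.7 points at ICC 0.10. A gap above 5 points in either direction then has probability 27% to 38%.

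**One property, not two.** Var(ANCOVA) + (1-r)²·Var(g) = (1-r²) + (1-r)² = 2(1-r) = Var(DiD). At r = 0.5 this is 0.75 + 0.25 = 1.00. The response to chance gaps is exactly where the extra variance comes from.

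**The case against.** The strongest reply is that DiD is unbiased over randomisations, so the choice is one of efficiency between two valid estimators. That stands. A reader might infer from the quasi-experimental label, or from the shift given a baseline gap, that the planned analysis is biased, or that over-correction is a further fault on top of wide intervals. The documents do not support either reading. Allocation is plainly disclosed as random, and the shift is the variance loss seen conditionally.

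Size is also open to challenge, and this stands too. No correlation is given, and at r = 0.9 the loss is only 1% to 3%.

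The formulas assume a linear scale, whereas Table 9 lists mostly percentages and a median. The direction carries over approximately, but the exact figures do not. Some outcomes fall outside the household panel:

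- The cost-effectiveness ratio has no baseline value to adjust for.
- Drug availability and prescribing are measured at the PHC.
- Exit interviews recruit patients as they leave and are not described as a panel.

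For PHC-level and exit-interview outcomes, the PHC's own baseline value can still be used.

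Finally, the covariate-adjusted regressions might already include the baseline outcome, and an article need not list every covariate. But the article does fix DiD as the effect test, in both the abstract and the analysis section. Adding fixed household or PHC characteristics as main effects to a DiD on complete pairs leaves its estimate unchanged. The stated aim of allowing for time and institutional factors does not require DiD either: concurrent randomised controls handle time, and randomisation balances institutional factors in expectation.

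**Conclusion.** The point holds as one of efficiency. The stated effect test is valid, but less precise than a baseline-adjusted endline model whenever r is below 1. On a linear scale the standard errors are about 24%, 15%, 8% and 3% larger at r of 0.3, 0.5, 0.7 and 0.9. Over the assumed range of r for PHC means (0.37 to 0.80) the excess is 21% down to 5%. The direction is secure; the size rests on assumed correlations, equal arms and equal variances, and is approximate for binary and median outcomes. The change is worth making because it needs no new data, but nothing here makes the planned results invalid.

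**What to change.** For outcomes measured at both surveys, state that the main effect estimate comes from a model of the endline outcome on arm, adjusted for the baseline value of the same outcome:

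- **Household outcomes:** the household's own baseline value and the PHC baseline mean.
- **Facility outcomes, and exit-interview outcomes if repeated at endline:** the PHC's baseline value.
- **Indicators defined as changes** (out-of-pocket expenditure, uptake of generics): model the endline value adjusted for baseline, not the change.
- **Clustering:** at the PHC, the randomised unit.
- **Incremental cost-effectiveness ratio:** outside this change.

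Keep DiD as a sensitivity analysis. The cost is a change of analysis wording, made before endline data are examined. Baseline values are already collected for the households and facilities surveyed.
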